## Abstract

**Background:**

Shoulder pain is the third most common reason for consultation with a physiotherapist and up to 26% of the general population might be expected to experience an episode at any one time. Disorders of the shoulder muscles and tendons (rotator cuff) are thought to be the commonest cause of this pain. The long-term outcome is frequently poor despite treatment. This means that many patients are exposed to more invasive treatment, e.g. surgery, and/or long-term pain and disability.

Patients with this disorder typically receive a course of physiotherapy which might include a range of treatments. Specifically the value of exercise against gravity or resistance (loaded exercise) in the treatment of tendon disorders is promising but appears to be under-used. Loaded exercise in other areas of the body has been favourably evaluated but further investigation is needed to evaluate the impact of these exercises in the shoulder and particularly the role of home based or supervised exercise versus usual treatment requiring clinic attendance.

**Methods/Design:**

A single-centre pragmatic unblinded parallel group randomised controlled trial will evaluate the effectiveness of a self-managed loaded exercise programme versus usual clinic based physiotherapy. A total of 210 study participants with a primary complaint of shoulder pain suggestive of a rotator cuff disorder will be recruited from NHS physiotherapy waiting lists and allocated to receive a programme of self-managed exercise or usual physiotherapy using a process of block randomisation with sealed opaque envelopes. Baseline assessment for shoulder pain, function and quality of life will be undertaken with the Shoulder Pain & Disability Index, the Patient Specific Functional Scale and the SF-36. Follow-up evaluations will be completed at 3, 6 and 12 months by postal questionnaire. Both interventions will be delivered by NHS Physiotherapist’s.

An economic analysis will be conducted from an NHS and Personal Social Services perspective to evaluate cost-effectiveness and a qualitative investigation will be undertaken to develop greater understanding of the experience of undertaking or prescribing exercise as a self-managed therapy.

**Trial registration number:**

ISRCTN84709751

## Background

Shoulder pain is one of the most common musculoskeletal symptoms with prevalence estimated at between 16 to 26% in the general population at any one time [1,2]. It is the third most common primary care musculoskeletal presentation [3] and the third most common reason for consultation with a physiotherapist [4]. Impaired shoulder function impacts significantly upon activities of daily living, including eating, dressing and working [5]. Disorders of the shoulder muscles and tendons (rotator cuff) are the commonest cause of this pain [6]. However long-term outcome is frequently poor for a significant proportion of patients which means that many are subsequently exposed to more invasive and costly treatment options, e.g. injections, surgery, and/or long-term pain and disability [7].

Shoulder pain, incorporating rotator cuff disorders, is a significant burden to the NHS and society. It has been identified that around 1% of adults in the UK consult their GP with a new presentation of shoulder pain each year. This amounts to over 500,000 adults. Costs in the first 6 months following primary care contact have been estimated to be €690 which means that costs attributable to this problem are in the region of €345 million or £310 million per year. Almost 50% of this cost is attributable to sick leave from paid employment [8]. Additionally, in 2005/6, 16,885 patients were admitted to hospital diagnosed with problems relating to the rotator cuff [9]. NHS costs associated with surgical procedures for such shoulder problems are estimated at £1,762 [10], which equates to a conservative estimate of almost £30 million per year. Clearly chronic rotator cuff disorders bring the associated health costs and economic burden, including loss of productivity, associated with other chronic conditions [5]. Therefore, this is an important health and social care problem for patients, clinicians, commissioners and researchers to consider.

Despite rotator cuff disorders being such a common shoulder problem there is a lack of high quality studies upon which to base practice [11]. Numerous systematic reviews have been undertaken in relation to subacromial impingement syndrome, an umbrella term encompassing rotator cuff disorders, investigating the various plausible interventions including physiotherapy, corticosteroid injections and surgery but all identify the insufficiency of the evidence base when attempting to draw conclusions [12-17]. Specifically in relation to the rotator cuff, a recent systematic review, which included 4 randomised controlled trials, suggested that loaded exercise, i.e. exercise against gravity or resistance, in the treatment of this disorder was promising [18] but due to the paucity of research and methodological limitations of the included studies further research is warranted. It was also recognised that home based or supervised exercise appears to confer similar outcomes to interventions, including therapist-led interventions, which were offered in a clinic-based setting. Additionally the benefits of loaded exercise have been reported in a particularly resistant patient group with long standing shoulder pain awaiting surgery due to a lack of response to previous conservative care [19]. Although small (n = 9), this uncontrolled pilot study reported that 56% responded to the point where they no longer required surgery despite a mean duration of pain of 41 months. Chronic rotator cuff tendon disorders have been shown to demonstrate similar pathological changes to tendon disorders in other areas of the body, e.g. the elbow, Achilles tendon, patellar tendon [20] where favourable results including reduced pain and improved function have been demonstrated in response to similar loaded exercise [21].

A recent survey of current practice suggests that physiotherapists usually offer a wide range of interventions for rotator cuff disorders including advice, stretching, exercise, manual therapy, massage, strapping, acupuncture, electrotherapy, corticosteroid injection [22]. The majority of UK physiotherapists would expect patients to engage with some level of self-management but more than 58% would ask the patient to return for therapist-led interventions. The variability in the approach of physiotherapists might reflect the lack of high quality evidence upon which practice can be based.

It is hypothesised that self-managed loaded exercise has the capacity to reduce costs associated with rotator cuff disorders and improve treatment outcome which therefore reduces the need for work absenteeism and further expensive invasive interventions. There is a clear need for high quality research in this area to inform clinical practice and commissioning priorities. At a time when healthcare agendas are emphasising the need to encourage the self-management of long-term conditions this research would build upon the developmental work that has been undertaken so far and, based upon high quality research methods, will offer useful clinical and cost data upon which practice can be developed and future research can be based.

## Methods/Design

### Aims

The proposed study aims to answer the question: Is a self-managed exercise programme more effective than usual physiotherapy for chronic rotator cuff disorders?

The objectives are:

· To evaluate clinical effectiveness of loaded exercise in terms of pain, function and well-being.

· To evaluate cost-effectiveness of the interventions.

· To investigate patient adherence with treatment.

· To explore the perceptions and experience of the study participants.

### Methods

The study design is a single-centre pragmatic unblinded parallel group randomised controlled trial (RCT) combined with qualitative investigation of patient and therapist experience. The study will be based at Doncaster & Bassetlaw Hospitals NHS Foundation Trust, UK.

The first part of the proposed study will be a RCT comparing self-managed loaded exercise versus usual physiotherapy.

### The intervention

The intervention is self-managed loaded (against gravity or resistance) exercise. The exercise, prescribed by the physiotherapist but completed by the patient independently, involves exercising the affected shoulder against gravity, a resistive therapeutic band or hand weight over 3 sets of 10 to 15 repetitions completed twice per day. This exercise can be uncomfortable for the patient but is prescribed to ensure that the discomfort is manageable. Exercise prescription is guided by symptomatic response requiring that pain is produced during exercise that remains no worse upon cessation of that exercise [7,23]. Hence participants with more severe symptoms tend to commence a lighter regime to begin with. A typical programme is presented in Box 1.

**Box 1 T1:** Typical loaded exercise progression

1. Week 0: Baseline assessment:
·Resisted isometric (no movement) shoulder abduction (taking the arm out to the side) against a wall, or
·Resisted shoulder abduction from 0 to 30° using moderate resistance from Theraband (resistive band used for training purposes).
2. Week 3: Initial follow-up:
·Resisted shoulder abduction from 80 to 120° using light weight, e.g. tin of food.
3. Week 6: Second follow-up:
·Resisted shoulder abduction from 80 to 120° with progressively increasing repetition and weight, e.g. heavy Theraband or dumbbell.
4. Week 12: Final follow-up/discharge.

To maintain the pragmatic value of the study, in both arms of the trial, the treating physiotherapists will determine the number of sessions, frequency and point of treatment cessation. However, the emphasis of the intervention arm is towards self-management with supervision and guidance only offered by the physiotherapist [7,23].

### The comparator

Usual physiotherapy might include a range of interventions including advice, stretching, exercise, manual therapy, massage, strapping, acupuncture, electrotherapy, corticosteroid injection at the discretion of the treating physiotherapist.

Prior to the recruitment of patients into the trial, the physiotherapists of Doncaster & Bassetlaw Hospitals NHS Foundation Trust who usually treat patients with rotator cuff disorders will be invited to participate in the study. A participant information sheet will be provided and explained via an initial information session delivered by the research team. If they wish to be included they will be asked to complete a consent form and return to the chief investigator within 2 weeks. During these training sessions the issue of contamination of the control arm and the implications will be discussed in an attempt to minimise contamination. The degree of any contamination will be evaluated via review of patient records and reported accordingly.

### Recruitment

Inclusion criteria will be: (i) Age ≫ 18 years, (ii) Willing and able to participate, (iii) Primary complaint of shoulder pain with or without referral into the upper limb for ≫ 3months, (iv) No/minimal resting shoulder pain, (v) Range of shoulder movement largely preserved, and (vi) Shoulder pain provoked consistently with resisted muscle tests, usually abduction or lateral rotation.

Exclusion criteria will be: (i) Shoulder surgery within last 6 months, (ii) Reasons to suspect systemic pathology including inflammatory disorders, (iii) Cervical repeated movement testing affects shoulder pain and/or range of movement. People who are unable to understand written and spoken English will be included in the study and NHS translation services will be accessed to accommodate their needs.

Potential trial participants will be identified from the NHS physiotherapy waiting list by a physiotherapist who usually has access to this information as part of their clinical role. Initial contact will be made through an introductory letter. Along with this letter the potential participants will also receive a participant information sheet and consent form. The letter will be followed up with a telephone call made by the physiotherapist one week later where further study information will be relayed as required and an enquiry about further participant involvement will be made. If the call recipient expresses interest in participating in the study the physiotherapist will then undertake initial telephone screening for inclusion criteria i to iv and exclusion criteria i to ii. If these criteria are met then the potential participant will be invited to read the participant information sheet, ask any questions and sign the consent form prior to attending for physical examination screening for inclusion criteria v to vi and exclusion criteria iii. If the participant does not wish to pursue the discussion or does not meet the criteria they will be thanked for their time and told that their referral will continue to be treated as per usual arrangements.

Physical examination screening will also be carried out by an experienced clinical physiotherapist. The physical examination screening will take up to 30 minutes and will include assessment of neck and shoulder movements and any associated symptomatic responses as per a typical musculoskeletal examination. If potential participants do not meet inclusion criteria v to vi they will be thanked for their time, offered advice about their presenting problem in line with the physical examination screening, e.g. advice to keep the arm moving, offered a generic advice leaflet produced by the Physiotherapy department at the Doncaster & Bassetlaw Hospitals NHS Foundation Trust and told that their referral will continue to be treated as per usual arrangements. This research study will not interfere with the timing of receiving physiotherapy. The process of including or excluding participants will take place whilst the referral remains on the waiting list.

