### Baseline/outcome assessment

After the participants have been assessed for eligibility and consent has been gained, prior to randomisation, they will complete a range of appropriate patient-reported outcome measures to establish baseline pain, function, quality of life and level of self-efficacy. Additionally, the participants’ preference for one treatment or the other, if they had a free choice, will be noted to enable analysis of the effect of preference on outcome.

The primary aim of the proposed study is to evaluate the clinical and cost-effectiveness of self-managed loaded exercise versus usual physiotherapy for rotator cuff disorders. The primary outcome measure will be the Shoulder Pain & Disability Index (SPADI) [24] score at 12 weeks. SPADI is a self-report measure specifically developed to evaluate pain and function in patients with shoulder pathology [25]. It is a commonly used measure which has been validated for use in this patient population and a minimally clinically important change of 10 points has been identified [25]. The SPADI includes 13 items divided into 2 sub-scales; pain (5 items), disability (8 items). The responses are indicated on a visual analogue scale where 0 = no pain/no difficulty and 10 = worst imaginable pain/so difficult it requires help. The items are summed and converted to a total score out of 100.

The Short-form 36 (SF-36) is a generic measure of health related quality of life [26] and is the most widely used measure of this nature. The SPADI & SF-36 will be repeated at 12, 24 and 52 weeks and returned by post. These measures will be complemented by the patient specific functional scale (PSFS) which is a patient-specific outcome measure which investigates functional status and is intended to complement the findings of generic or condition-specific measures [27]. The PSFS has been shown to be valid and responsive in various musculoskeletal populations [28]. Due to the nature of the PSFS, this measure will be completed at baseline and then completed, until the end of the treatment episode, in the presence of the attending physiotherapist. Treatment duration is likely to be in the region of 3 months with the PSFS being completed at 1, 2 and 3 months post baseline.

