### Randomisation

Block randomisation will be carried out by an administrator based in the physiotherapy department but independent to the study. Following receipt of written informed consent and baseline assessment, a computer generated random number sequence indicating group allocation will be concealed in sealed opaque envelopes which will be consecutively numbered. The group allocation and baseline PSFS assessment will be attached to the patient referral for the attention of the treating physiotherapist in readiness for the programme of treatment.

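### Baseline is taken on the waiting list while Box 1 starts its week 0 at the first exercise session, so the 12-week primary SPADI can include untreated time and precede the end of a typical programme

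*Protocol article*

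**What the plan says.** All places are in the protocol article, Methods/Design.

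- **Recruitment.** "Potential trial participants will be identified from the NHS physiotherapy waiting list". Screening is done before the patient leaves that list: "The process of including or excluding participants will take place whilst the referral remains on the waiting list". The usual wait is left as it is: "This research study will not interfere with the timing of receiving physiotherapy".
- **Baseline/outcome assessment.** Patients fill in the baseline questionnaires once eligibility and consent are settled and before they are randomised. The primary outcome is the SPADI at 12 weeks, and SPADI and SF-36 come back by post at 12, 24 and 52 weeks. For the PSFS the time origin is explicit: "Treatment duration is likely to be in the region of 3 months with the PSFS being completed at 1, 2 and 3 months post baseline".
- **Randomisation.** Allocation follows consent and baseline. "The group allocation and baseline PSFS assessment will be attached to the patient referral for the attention of the treating physiotherapist", so that it is there before treatment begins.
- **Data analysis.** SPADI and SF-36 are listed as taken at baseline and then at weeks 12, 24 and 52.
- **The intervention, Box 1.** Week 0 carries the label of baseline assessment and already lists exercises. Progressions follow at weeks 3 and 6, and the last entry is "4. Week 12: Final follow-up/discharge".
- **Sample size calculation.** Difference 10 points, SD 24, 80% power, two-sided 5%, 91 per group.

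**The concern.** The article contains two week 0s. In Box 1, baseline and first exercise are the same occasion. In the recruitment, baseline and randomisation text, baseline is completed by someone who is still waiting for treatment, and the trial does nothing to bring the first session closer. The article neither ties baseline or randomisation to the first session nor limits the gap between them.

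If follow-up runs from the waiting-list baseline, the primary measurement compares two courses of treatment at a point when some patients have not finished them. Untreated time shortens exposure in both arms and adds patient-to-patient variation in how much treatment the 12-week score reflects. The sample size makes no allowance for a smaller difference at that point. The AUC and QALY summaries, which start from the same baseline, would absorb the wait as well.

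**Working it through.** **1. Order of events.**

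| Step | Waiting-list text | Box 1 |
|---|---|---|
| Baseline | After eligibility and consent, before randomisation, before treatment | Week 0 |
| First exercise | After the usual wait, w weeks later (w not given) | Week 0 |
| End of typical programme | About week 12 + w from baseline | Week 12 |
| Primary SPADI | Week 12 | Week 12 |

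The two columns agree only if w = 0. The PSFS shows the same tension. It is completed with the attending physiotherapist at months 1, 2 and 3 after baseline, alongside treatment of about 3 months. That works only if baseline and first session are close together.

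**2. The plan's own figure.** Inputs from Sample size calculation: δ = 10, σ = 24, two-sided 5%, 80% power.

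n = 2σ²(1.96 + 0.8416)² / δ² = 2 × 576 × 7.849 / 100 = 90.4, rounded up to 91 per group. This matches the stated number.

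Standard error of the difference with 91 per group: 24 × √(2/91) = 3.558. Power = Φ(10/3.558 − 1.96) = Φ(0.851) = 80%.

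**3. Treated time at the primary endpoint.** With a wait of w weeks, treated time at week 12 is 12 − w. The documents do not give w, so the values below are assumed.

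**4. Illustration of dilution.** Second assumption, also not in the documents: the between-arm difference grows linearly to 10 points over 12 treated weeks. Then D(w) = 10 × (12 − w)/12 and power = Φ(D(w)/3.558 − 1.96).

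| Wait w (weeks) | Treated weeks | Difference at week 12 | Power, 91 per group |
|---|---|---|---|
| 0 | 12 | 10.0 | 80% |
| 1 | 11 | 9.2 | 73% |
| 2 | 10 | 8.3 | 65% |
| 3 | 9 | 7.5 | 56% |
| 4 | 8 | 6.7 | 47% |
| 6 | 6 | 5.0 | 29% |

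The t-test versions differ by about one point or less (79.8%, 64.4%, 55.4%, 46.2% and 28.7% at waits of 0, 2, 3, 4 and 6 weeks).

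**5. Sensitivity to the shape.** If the full 10 points were instead reached within the first 6 treated weeks and then held, a wait of up to 6 weeks would leave at least 12 − 6 = 6 treated weeks, the difference would stay at 10 and power at 80%. At a 6-week wait the loss therefore runs from none to the 29% in the table between these two shapes.

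**6. Later assessments.** With a 6-week wait, week 24 falls 24 − 6 = 18 weeks after the first session, past the end of a 12-week programme.

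**The case against.** The strongest reply is that time zero for the SPADI is never actually stated. Counting from baseline is explicit only for the PSFS, and the dispatch date of postal questionnaires is something that a full protocol might settle. The sentence about the waiting list concerns screening; that baseline and randomisation also precede treatment follows from the order of steps, not from a stated interval. The PSFS schedule and Box 1 suggest that the authors expected a short wait. Box 1 is only a typical programme, and the physiotherapist decides treatment length in both arms, so some patients would still be in treatment at week 12 even without a wait.

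Much of this stands, and it limits the wording to *can fall before*. It does not remove the point. The conflict lies between statements that the article does make, and an expected short wait is not secured by a design that leaves treatment timing untouched.

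A reader might infer more than the documents support:

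- *That the trial has 29% power.* This needs an assumed wait and an assumed linear build-up.
- *That a null result could not be told apart from measuring too early.* SPADI is repeated at 24 and 52 weeks and summarised by AUC, so a later effect could be seen there, though not on the primary endpoint.
- *That the comparison is biased.* The wait follows randomisation and applies to both arms. Nothing indicates that it would differ by arm.
- *That the essential part of the intervention starts only at week 6.* Box 1 has resisted exercise from week 0 and a light weight from week 3, and nothing singles out the week-6 progression.
- *That keeping patients who never start treatment is a flaw.* It is what the stated intention-to-treat analysis requires.

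**Conclusion.** The point holds as a timing conflict that a cheap design change would remove. Read naturally, the schedule runs from a baseline completed on the waiting list, while Box 1 runs from the first session. For any patient with a wait above zero, the primary SPADI then includes untreated time and can precede the end of a programme of about 12 weeks. The likely effect is a diluted contrast and extra noise in both arms, not a bias between them.

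The size cannot be established from the article. It depends on the wait, which is not given, and on how quickly the difference between arms develops. The power figures show what could be lost under one stated shape and are no estimate for this trial. The stated 91 per group is correct on its own inputs and stays correct if the 12 weeks are counted from first treatment.

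**What to change.** 1. Reconcile Recruitment, Baseline/outcome assessment, Randomisation, Data analysis and Box 1 on a single time zero, and name it for the 12-, 24- and 52-week assessments and for the PSFS.
2. Keep screening and consent on the waiting list. Complete the baseline measures and open the envelope only once the first appointment date is fixed, and shortly before it, leaving enough time to notify the treating physiotherapist.
3. Count 12, 24 and 52 weeks from that pre-fixed date in both arms, whether or not the visit is kept. Because the date is set before allocation, assessment timing cannot depend on arm, and intention-to-treat is preserved.
4. Record and report the time from randomisation to first session by arm.

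This moves the assessments and the envelope, not the treatment, so the commitment not to affect the timing of physiotherapy is kept. The cost is protocol wording, some scheduling work for the independent administrator, slightly later baseline forms, and a few consented patients lost before randomisation instead of after it.
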